**Secondary objectives:**

- - - Assessment of the beta cell insulin response to oral and intravenous glucose loads early and 1 year after gastric bypass surgery including the quantification of the incretin effect using oral and isoglycaemic intravenous glucose infusion tests
    - Relation of early and long-term changes in beta cell function to changes in parameters of adipoinsular and enteroinsular axes in severely obese patients with and without T2DM
    - Comparison of the changes in adipoinsular and enteroinsular axes after weight loss achieved after gastric bypass with BMI-matched non-bariatric controls

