# Methodology

## Population

Bariatric group: 85 severely obese patients (55 T2DM patients and 30 non-diabetic [non-DM] patients) fulfilling the indication criteria for laparoscopic gastric bypass surgery including the personal wish to undergo gastric bypass will be consecutively recruited at the Obesity Outpatient Clinic, Medical University Graz, Austria and at Interdisciplinary Obesity Center in St. Gallen, Switzerland. In the subgroup of T2DM surgery patients, patients with wide range of disease duration will be included. Long-standing T2DM will be classified as the disease duration longer than 10 years at the time of surgery. Within the T2DM subgroup, the expected proportion of long-standing T2DM will be 40-50%. For the detailed recruitment proportions at both sites see Table 1.

Control group: 30 patients (15 T2DM patients and 15 non-DM patients) undergoing elective laparoscopic abdominal surgery in the absence of neoplastic disease, acute or chronic inflammatory disease will be consecutively recruited at both sites. The control group will be matched with bariatric group for age, sex and expected one-year postoperative BMI (BMI 27-35 kg/m^2^).

| Site | **Bariatric group (n=85)** | | **Control group (n=30)**  **(15 T2DM / 15 non-DM)** |
| --- | --- | --- | --- |
|  | **T2DM** | **non-DM** |  |
| Graz, Austria | 15 | 15 | 15 |
| St. Gallen, Switzerland | 40 | 15 | 15 |
| Total | 55 | 30 | 30 |

*Table 1. Recruitment proportions at both sites.*

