## Protocol

This double-center, prospective, controlled, longitudinal open clinical trial will be performed at Department of Endocrinology and Nuclear Medicine, Medical University Graz, Austria and at Interdisciplinary Obesity Center, Kantonsspital St. Gallen, Switzerland. Both centers will follow the same protocol. Both bariatric and control group will be examined at baseline before surgery. During surgical procedure samples of subcutaneous (SAT) and visceral (VAT) adipose tissue will be obtained. In bariatric patients, repeated follow-up visits will be arranged at 1-2 weeks and 12 months after the surgery and a needle biopsy of SAT will be performed at 12-months follow-up. Control group will be examined at baseline only.

At baseline visit detailed medical history and concomitant medication, particularly diabetes duration and history of diabetes therapy will be recorded. To verify the information on diabetes history the patient’s family physician will be contacted by phone calls.

At baseline and all follow-up visits, patients and controls will be studied on three occasions after an overnight fast and procedures will be grouped as follows:

1. Biochemistry, anthropometry, vital signs and oral glucose tolerance test (visits 1,4,7)
2. Isoglycaemic intravenous glucose infusion, vital signs (visits 2,5,8)
3. Botnia clamp, vital signs (visits 3, 6 and 9) and needle biopsy of SAT (visit 9)

For study visit and procedure schedule see Table 2.

| **Groups** | **Procedure** | **Baseline** | | | **1-2 weeks** | | | **12 months** | | |
| --- | --- | --- | --- | --- | --- | --- | --- | --- | --- | --- |
|  |  | **V1** | **V2** | **V3** | **V4** | **V5** | **V6** | **V7** | **V8** | **V9** |
| Bariatric group  (n=85)  55 T2DM/30 non-DM | Medical history | x |  |  | x |  |  | x |  |  |
|  | Vital signs | x | x | x | x | x | x | x | x | x |
|  | Biochemistry | x |  |  | x |  |  | x |  |  |
|  | Anthropometry | x |  |  | x |  |  | x |  |  |
|  | OGTT | x |  |  | x |  |  | x |  |  |
|  | Isoglyc. iv.infusion |  | x |  |  | x |  |  | x |  |
|  | Botnia clamp |  |  | x |  |  | x |  |  | x |
|  | SAT needle biopsy |  |  |  |  |  |  |  |  | x |
| Control group  (non-bariatric abdominal surgery)  (n=30)  15 T2DM/15 non-DM | Medical history | x |  |  |  |  |  |  |  |  |
|  | Vital signs | x | x |  |  |  |  |  |  |  |
|  | Biochemistry | x |  |  |  |  |  |  |  |  |
|  | Anthropometry | x |  |  |  |  |  |  |  |  |
|  | OGTT | x |  |  |  |  |  |  |  |  |

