## 6. Statistical analysis

All data will be checked for distribution normality. In case of non-Gaussian distribution, log transformed data will be assured for further statistical evaluation.

1. Changes in beta cell function and other variables after gastric bypass surgery will be assessed by analysis of variance (ANOVA) with repeated measures. ANOVA models will include following factors:
   1. group factor as the between-subject factor (comparison between groups of bariatric patients with short- and long-standing T2DM and bariatric patients without T2DM)
   2. time factor (repeated measurements at baseline and two follow-up visits)
   3. treatment factor if appropriate - in case of repeated measurements within 1 follow-up (eg. GLP-1 profile during OGTT, basal + insulin-stimulated concentrations of adipokines and cytokines)

Time and treatment factors as the within-subject factors account for the repetition in the ANOVA model.

1. Relations between changes in beta cell function and clinical characteristics or changes in parameters of adipoinsular and enteroinsular axes will be evaluated using multivariate regression analyses.
2. For comparison of beta cell function and other variables after weight loss achieved following gastric bypass with results from BMI-matched non-bariatric controls, Mann-Whitney *U* test will be used.

Based of foregoing studies [10, 11, 19-21] a sample size of at least 15 subjects per subgroup can be safely expected to provide a sufficient statistical power to detect meaningful changes in beta cell function. Our sample size is based on feasible recruitment expectations at both sites: total number of 85 patients with an estimated drop-out rate of 10-12% during the follow-up, giving the final sample size of 75 patients – 50 patients with T2DM (among them approx. 40-50% with long-standing T2DM) and 25 patients without T2DM.

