# Novelty and importance of the proposed work

For the first time, our study will systematically evaluate beta cell function, by using three different glucose stimulation tests, in relation to adipoinsular and enteroinsular axes early and long-term after gastric bypass. Moreover, our study will also address the important question, if surgery induced beta cell function improvement also occurs after longer duration of T2DM when reduction of beta cell mass is expected. The parallel performance of an OGTT and an isoglycemic iv. glucose infusion will allow to quantify the incretin effects and thus, to precisely define the role of incretin hormones in the improvement of beta cell function after bariatric surgery. Our findings are therefore expected to bring new knowledge on possible reversibility of beta cell damage in long-standing T2DM.

Our approach of repeated biopsy at 1 year follow-up and comparison with control group matched for expected one-year postoperative BMI shall enable to identify surgery-specific changes in gene expression in adipose tissue independent on weight loss.

The sample size of this double-centre study which also includes controls will enable to achieve sufficient power of the study to reliably detect significant differences between groups as well as to perform valid multivariate regression analysis.

It is worth to point out that only the combined effort of our two study centres will let us achieve such a large sample size recruited in an acceptable period of time.

The results are expected to provide important new insight into the pathophysiology of disturbed beta cell function and its possible restoration in T2DM. Bariatric operations such as the gastric bypass procedure provide a unique model of rapid changes in pathological beta cell function and the results of this study on the long run may help to develop rational approaches to overcome beta cell failure in T2DM also with conservative means, e.g. by pharmacotherapy.

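### The secondary bypass-versus-control comparison is unadjusted and uses controls measured once with no planned weight loss, so it cannot compare changes or isolate surgery-specific adipose gene expression from weight loss

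*Protocol*

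**What the plan says.** The secondary objectives in the Protocol include "Comparison of the changes in adipoinsular and enteroinsular axes after weight loss achieved after gastric bypass with BMI-matched non-bariatric controls".

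The Population section describes the controls as "30 patients (15 T2DM patients and 15 non-DM patients) undergoing elective laparoscopic abdominal surgery" and states: "The control group will be matched with bariatric group for age, sex and expected one-year postoperative BMI", with a range of 27-35 kg/m². The bariatric group is "85 severely obese patients (55 T2DM patients and 30 non-diabetic [non-DM] patients".

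The section headed Protocol fixes the controls' visits: "Control group will be examined at baseline only". Table 2 agrees, with no control entries at 1-2 weeks or 12 months. Bypass patients have anthropometry, including BMI, again at 12 months (visit 7).

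Under Procedures, subcutaneous and visceral fat is taken during the operation in both groups. At 12 months, bypass patients have a needle biopsy of subcutaneous fat only.

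Section 6 (Statistical analysis) assigns the comparison "with results from BMI-matched non-bariatric controls, Mann-Whitney" U. It names no covariates and does not say whether the test is run within diabetes status or across it.

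The Novelty section says that the repeat biopsy and this control group "shall enable to identify surgery-specific changes in gene expression in adipose tissue independent on weight loss".

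**The concern.** Three things do not fit together.

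- **Objective against schedule.** A comparison of changes needs two time points in each group. Controls have one.
- **Claim against design.** Isolating surgery from weight loss needs a comparator that lost weight without bypass. A control at BMI 31 need not have lost any weight, whereas a bypass patient at BMI 31 has. At equal BMI the contrast mixes the operation with having lost weight. For gene expression it also mixes in the way the fat was sampled.
- **Test against available data.** A two-sample rank test cannot use achieved BMI, diabetes status or site, all of which are recorded and may differ between the groups.

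At stake is the interpretation of a secondary objective and of the gene-expression claim. A difference in diabetes mix, BMI, site, sampling technique or weight history could be read as an effect of bypass.

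**Working it through.** **1. The plan's own figures.** Section 6 goes from 85 recruited to 75 followed (50 T2DM, 25 without), with "an estimated drop-out rate of 10-12% during the follow-up".

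- Total: 85 × 0.90 = 76.5 and 85 × 0.88 = 74.8, against 75.
- T2DM: 55 × 0.90 = 49.5 and 55 × 0.88 = 48.4, against 50.
- Non-diabetic: 30 × 0.90 = 27.0 and 30 × 0.88 = 26.4, against 25.

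These reproduce to within two patients. No sample size, power or effect size is stated for the control comparison.

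**2. Balance of the groups.**

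| | Bypass | Control |
| --- | --- | --- |
| T2DM (bypass: expected at 12 months) | 50/75 = 67% | 15/30 = 50% |
| Graz (Table 1, recruited) | 30/85 = 35% | 15/30 = 50% |
| BMI basis | achieved, measured at 12 months | chosen to fit an expected range |
| Time points | three | one |
| Fat sample for the 12-month contrast | needle, subcutaneous | intraoperative, subcutaneous |
| Planned weight loss | yes | none |

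The last three rows cannot be changed by any choice of test. The change in subcutaneous fat within bypass patients has the same sampling problem: intraoperative at baseline, needle at 12 months. There is no 12-month visceral sample.

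**3. Diabetes mix, if the test were pooled.** Suppose no surgery effect within either stratum and a T2DM/non-diabetic gap of D standard deviations. The protocol gives no value for D. The spurious mean difference is (0.667 − 0.500) × D = 0.167 D. A simulation of the two-sided Mann-Whitney test at 0.05 (20,000 runs, 50 + 25 against 15 + 15, normal outcome, SD 1 within stratum) gives:

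| D (SD) | Spurious shift, 0.167 D (SD) | False-positive rate |
| --- | --- | --- |
| 0 | 0 | 5.0% |
| 0.5 | 0.08 | 6.0% |
| 1 | 0.17 | 8.0% |
| 1.5 | 0.25 | 10.0% |
| 2 | 0.33 | 11.4% |

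With equal drop-out in both diabetes groups the bypass mix would be 55/85 = 65%, and the shift slightly smaller: 0.147 D.

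**4. The same comparison within strata.** The bias in step 3 is then zero, but precision falls. The detectable difference at 80% power is (1.96 + 0.84) × √(1/n₁ + 1/n₂) ÷ √(3/π), the last term being the efficiency of the rank test for normal data:

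- pooled, 75 against 30: 2.80 × 0.216 ÷ 0.977 = 0.62 SD
- T2DM, 50 against 15: 2.80 × 0.294 ÷ 0.977 = 0.84 SD
- non-diabetic, 25 against 15: 2.80 × 0.327 ÷ 0.977 = 0.94 SD

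**5. BMI mismatch (illustration only).** The protocol gives no BMI distribution or slope. Assume a BMI SD of 4 kg/m², an outcome-BMI correlation of 0.3-0.5 and a mean mismatch of 1-2 kg/m². Bias = correlation × mismatch ÷ SD, from 0.3 × 1 ÷ 4 = 0.075 SD to 0.5 × 2 ÷ 4 = 0.25 SD. With a standard error of 0.216 (normal approximation, both tails counted) a 5% test would reject in about 6% to 21% of trials with no surgery effect. With no mean mismatch, this bias is zero.

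**The case against.** The strongest reply has four parts.

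- **Pooling is not stated.** A reader might infer it from the bare Mann-Whitney sentence, but the document does not say so. The 15/15 control split, the objective separating patients with and without T2DM, and the remark about at least 15 subjects per subgroup all fit a stratified comparison. Strata may also be set in a statistical analysis plan that is not at hand. This stands, so the 6-11% is conditional and is not a property of the plan.
- **Matching covers more than BMI.** A reader might take the phrase BMI-matched in section 6 to mean BMI alone, but age and sex are also matching variables. Achieved BMI cannot be known when controls are recruited, so matching on an expected value is reasonable. This stands for the design. It does not explain why the analysis should leave out the BMI that is later measured.
- **The claim is narrow.** The surgery-specific wording occurs once, in the Novelty section, for adipose gene expression only. Extending it to incretins, circulating adipokines or beta cell function would go beyond the text. Section 6 itself speaks of results after weight loss, which can be read as levels.
- **A model does not cure the main defect.** Covariates cannot separate surgery from prior weight loss, or needle from intraoperative sampling. This is right, and it is why the wording must change as well as the test.

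What the reply does not answer is that controls have one time point and no planned weight loss. The stated objective and the stated inference are therefore unavailable under any analysis.

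**Conclusion.** The point holds in a limited form. From the text alone, without assumptions:

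- changes cannot be compared with controls who are measured once;
- the gene-expression inference is not identified, because surgery, prior weight loss and biopsy technique all differ between the groups together;
- the named test cannot use achieved BMI, diabetes status or site.

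The numerical sizes are conditional. The 6-11% false-positive rate needs both pooling over diabetes status and an assumed gap of 0.5-2 SD, and it vanishes within strata. The BMI figures rest wholly on assumed values.

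A reader might go further and conclude that the trial's main result is compromised. It is not: the primary comparison of AIR between short- and long-standing T2DM does not use the controls.

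**What to change.** 1. **Analysis (section 6).** Replace the Mann-Whitney test with a linear model on the log- or rank-transformed outcome. Include group, pre-operative diabetes status, achieved BMI (at 12 months for bypass patients, at examination for controls), age, sex and site. Also report the comparison within the T2DM and non-diabetic strata.
2. **Secondary objective.** Reword it as a comparison of 12-month levels in bypass patients with the single level measured in controls.
3. **Novelty section.** Replace the claim with differences from BMI-matched controls not studied after weight loss. State that surgery, prior weight loss and biopsy technique cannot be separated, and that adjustment does not remove this limitation.

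The cost is five covariate degrees of freedom on about 75 + 30 = 105 patients, lower precision within strata (detectable differences of 0.84 and 0.94 SD instead of 0.62 SD), and a weaker stated claim. No additional patients, visits or measurements are needed.

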# Novelty and importance of the proposed work

For the first time, our study will systematically evaluate beta cell function, by using three different glucose stimulation tests, in relation to adipoinsular and enteroinsular axes early and long-term after gastric bypass. Moreover, our study will also address the important question, if surgery induced beta cell function improvement also occurs after longer duration of T2DM when reduction of beta cell mass is expected. The parallel performance of an OGTT and an isoglycemic iv. glucose infusion will allow to quantify the incretin effects and thus, to precisely define the role of incretin hormones in the improvement of beta cell function after bariatric surgery. Our findings are therefore expected to bring new knowledge on possible reversibility of beta cell damage in long-standing T2DM.

Our approach of repeated biopsy at 1 year follow-up and comparison with control group matched for expected one-year postoperative BMI shall enable to identify surgery-specific changes in gene expression in adipose tissue independent on weight loss.

The sample size of this double-centre study which also includes controls will enable to achieve sufficient power of the study to reliably detect significant differences between groups as well as to perform valid multivariate regression analysis.

It is worth to point out that only the combined effort of our two study centres will let us achieve such a large sample size recruited in an acceptable period of time.

The results are expected to provide important new insight into the pathophysiology of disturbed beta cell function and its possible restoration in T2DM. Bariatric operations such as the gastric bypass procedure provide a unique model of rapid changes in pathological beta cell function and the results of this study on the long run may help to develop rational approaches to overcome beta cell failure in T2DM also with conservative means, e.g. by pharmacotherapy.

# Facilities available

**Department of Endocrinology and Nuclear Medicine, Medical University of Graz, Austria**

As an integral part of Medical University of Graz and adjacent University Clinics, the Department of Endocrinology and Nuclear Medicine (Head: [name]) includes in- and outpatient facilities, which cover complex medical care for endocrine and metabolic diseases, including treatment of severe obesity. The Outpatient Clinic provides medical consultations for treatment of all endocrine diseases including diabetes, obesity and their complications, patient education and counselling programs. The health care for patients with severe obesity proceeds in close collaboration with the Department of General Surgery of Medical University Graz (Head: [name]) ensuring comprehensive bariatric care.

The broad research scopes of the department span from bone and calcium metabolism and osteoporosis, over polycystic ovary syndrome, sex and thyroid hormones issues, to the pathophysiology of metabolism, diabetes mellitus and obesity and their complications. Further research focuses on the development of new research technologies in diabetes and metabolism (open-flow microperfusion, clamp techniques, tracer techniques) and on the investigation of new pharmaceutical approaches for the treatment of diabetes mellitus.

**Clinical Research Centre, Medical University of Graz, Austria**

Complex research facilities for investigations in humans are available in the Clinical Research Centre (CRC) at the Centre for Medical Research, Medical University of Graz. The presented study will be performed in the CRC, where the developed infrastructure is available to conduct the human experimental studies in accordance with GCP guidelines. The Department of Endocrinology and Nuclear Medicine has full access to all facilities of the Clinical Research Centre.

**Laboratory for Endocrinology and Metabolism, and EndoGenLab, Medical University of Graz, Austria**

On the basis of the Laboratory for Endocrinology and Metabolism (Head: [name]), founded in 1962, the Laboratory for biochemical and molecular aspects of endocrine diseases (EndoGenLab) has been certified and acknowledged as a genetic laboratory by the Austrian Ministry and by the Austrian Society for Quality Control (ISO 9008 certification, first in 2006). The qualified staff is performing analyses of biochemical as well as genetic parameters and functional endocrine tests for scientific and routine purposes. The established methods include immunochemical analysis for endocrine and metabolic parameters (ELISA, RIA, LIA), gene expression analysis via real-time PCR or SNP genotyping. The annual output is about 250.000 tests in all fields of hormonal and metabolic analyses.

**Interdisciplinary Obesity Center, St.Gallen, Switzerland**

The Interdisciplinary Obesity Center St. Gallen offers the full range of up-to-date obesity therapy spanning from psychotherapy to bariatric surgery. Every year about 400 new patients report to the Interdiscipilnäry Obesity Center of whom approximately 160 undergo an bariatric operation. Currently, about 1000 operated patients are included in a multiprofessional structured follow-up programme. On background, the applicant from St. Gallen has an extented clinical experience in the management of obese and especially bariatric patients.

**Research laboratory of the Interdisciplinary Obesity Center, St. Gallen, Switzerland**

The obesity research laboratory (Head: [name]) is equipped with a wide range of technical facilities to perform comprehensive metabolic and biopsychological characterisation studies in bariatric and non-bariatric patients. The obesity research laboratory is joint with the Medical Research Center (Head: [name]) as well as with the Clinical Trial Unit (funded by the Swiss National Foundation; Head: [name]) of the Kantonsspital St. Gallen, and thus surrounded by other high quality research facilities. The main focus of the obesity research laboratory is to performed human experimental studies in the field of obesity and diabetes in accordance with GCP guidelines.

# Collaborative arrangements

**The Biobank of the Medical University of Graz, Austria** is specifically designed to support the needs of systems biology approaches to human diseases, drug discovery and public health. It is a research core facility of Medical University of Graz, which builds on different collections of human biomaterial (Blood, DNA, RNA, FFPE, Cryotissue, placenta, etc.) and represents a unique combination of Population-based biobank and Disease-based biobank. It comprehends one of the world's largest most consistent collection of diseased human tissues of the Institute of Pathology (healthy and diseased tissue, containing 3.3 million tissue samples from more than 880,000 patients) and one of the European one-of-a-kind oncology serum bank (400000 samples from app. 100000 patients in follow-up). The biobank will be further developed into a biological resource centre putting specific emphasis on standardization, international networking and the ethical, legal and societal issues (ELSI) of biobanking.

Based on systematic experimental evidence, best practice guidelines for sample-preservation and pre-analytical processing for intervention studies, sample collection standards will be developed specifically for the planned study, addressing the needs of collaboration of two centres.

The letter of confirmation is attached as Appendix 5.

